
**Fig. 1 Fig1:**
[figure not shown]
RCT intervention designs

### Participants and recruitment

The participants will be recruited from various organizations in Slovenia partnered with the leading institution and through different media channels. The intervention will also be advertised through university newsletters and webpages as well as a well-known Slovenian mental health platform. Interested participants will be able to apply for the study via an online form. Although we will not specifically exclude any professions, employees with knowledge-intensive jobs and high-stress occupations will be primarily targeted [44]. The recruitment stage will begin in August 2020. Following previous intervention studies in the workplace context (e.g., [17, 18]), participants will be pre-screened for eligibility. They will have to meet the following inclusion criteria: 1) being aged 18 or above, 2) working a minimum of 40 h per week and currently not on sick leave, 3) ability to commit (at least) 2 h per week to the online training, 4) ongoing internet connection and computer accessibility, 5) reporting difficulties with psychological detachment from work and burnout at least to a moderate extent. Participants undergoing other forms of treatment (psychotherapy, pharmacotherapy) or who have a clinical diagnosis of mental illness will not be eligible to participate. They will, however, receive additional information on relevant health care services and a link to mindfulness and CBT exercises they can practice on their own. Those eligible to participate will receive detailed information about the intervention and an online informed consent form. Participants who will commit to the study will be randomly assigned to one of the three groups. Following the approach by Querstret and colleagues [17], block randomization based on gender will be used. Participants will be randomized within blocks in such a way that an equal number of females and males are assigned to each of the groups because women exhibit more rumination and difficulties detaching from work at home (e.g., [17]). In order to control for expectations about potential benefits of the interventions, participants will be blinded to the intervention. Both the CBT-based and the MBSR intervention will be advertised as occupational stress-reduction interventions. The participants assigned to the waitlist control group will only be asked to participate in the study and fill out the questionnaires. They will also receive information regarding the delayed starting date of the training.

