## Methods/design

### Study design

The randomized controlled trial will follow the recommendations of the CONSORT (Consolidated Standards of Reporting Trials) group, which is considered a gold standard in clinical practice regarding devising interventions as well as their reporting [43]. The study design is depicted in Fig. 1. The study will take place between October 2020 and February 2021. In order to reach the target sample size, the second round of data collection will take place between January 2021 and May 2021, and additional rounds of data collection will be carried out if needed. Data collection in both intervention groups (i.e., CBT- and MBSR protocol) and the control group will be carried out immediately before (T1) and after the intervention (T2). During the 6-week intervention period, weekly questionnaires will be sent out to participants. The follow-up data collection will take place 3 months after the end of the intervention (T3). During T1, T2 and T3, participants will be asked to fill out questionnaires addressing all studied constructs, whereas the weekly questionnaire will only encompass the central mechanisms and primary study outcomes (i.e., work-related maladaptive thinking patterns, mindfulness, psychological detachment, and burnout). During the intervention period, participants from both intervention groups will receive e-mail notifications every Monday and Thursday with information about the assignments and exercises. The initial e-mail will include instructions on how to access the online platform with CBT and MBSR exercises. The notification every Monday will remind participants to fill out the weekly questionnaire before they start with the new exercise. All exercises from previous weeks will be visible on the online platform. Upcoming exercises will not yet be available to ensure that participants will not skip the activities or perform them in random order. The online platform will automatically monitor whether the participants followed the instructions and performed the respective exercises. In case of non-compliance, reminders will be sent out the following day. After the intervention, participants from the waitlist control groups will receive access to the online platform and all intervention materials, which they can perform in any order. They will receive weekly e-mails reminding them to perform the exercises and encouraging them to practice them. After the intervention, each participant will have the opportunity to request individualized feedback on his or her results.

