
Notwithstanding these limitations, the proposed intervention study is one of the first that is explicitly directed at comparisons between two protocols and mechanisms of change. Both notions are important, as the results may inform theory about psychological detachment and lead to the identification of decisive intervention ingredients. With the focus on work-related maladaptive thinking patterns [40, 84], the work-related well-being literature will potentially gain understanding of a new yet poorly understood, personal vulnerability factor that makes employees more susceptible to ill-being at work or even psychological disorders. Another strength of the intervention is the control of relevant confounding factors. Although the online intervention design may have some drawbacks, the contamination of experimental and control groups will not be a cause for concerns. As participants will not be recruited from one or a small number of organizations and will individually apply for the study, exchanges between participants from different intervention groups are not likely. Given the online protocol, intervention effects also cannot be attributed to positive and supportive interactions between participants [14]. As participants will be blinded to the intervention, the possibility of attenuated or accentuated intervention effects due to participants’ expectations will be minimal. Finally, both online interventions can be utilized by a wide range of professions and can easily be adapted to different workplace contexts and work schedules. The weekly monitoring of effects will further help to customize and shorten similar interventions in the future. As such, the protocol has the potential to significantly advance knowledge about evidence-based CBT and mindfulness interventions and holds promise to be highly applicable to organizational settings.

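### The article's wording points to the self-reported T1 baseline being collected after allocation, and nothing in it protects T1 from waitlist members already knowing their arm

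*Protocol article*

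**What the plan says.** In the Protocol article, Participants and recruitment gives the enrolment steps in this order:

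- Applicants are pre-screened. Then: "Those eligible to participate will receive detailed information about the intervention and an online informed consent form".
- Next: "Participants who will commit to the study will be randomly assigned to one of the three groups".
- On the control arm: "The participants assigned to the waitlist control group will only be asked to participate in the study and fill out the questionnaires". And: "They will also receive information regarding the delayed starting date of the training".

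Study design gives the timing of the baseline: "Data collection in both intervention groups (i.e., CBT- and MBSR protocol) and the control group will be carried out immediately before (T1").

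The same recruitment section says that "participants will be blinded to the intervention". The means described is that both active programmes are advertised alike, as stress-reduction programmes. Strengths and limitations concludes that "the possibility of attenuated or accentuated intervention effects due to participants’ expectations will be minimal".

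Under Measures, burnout and detachment are also collected at pre-screening. Under Effect evaluation, each of the two primary outcomes is analysed by a repeated measures ANOVA with three groups and three time levels (pre, post, follow-up). T1 is the pre level; the screening score is not used.

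**The concern.** Both primary outcomes are questionnaires about how people feel and unwind. Someone who has just learned that the training starts later may answer differently from someone about to begin. The blinding device can hide which of two similarly advertised programmes a person has. It cannot hide waitlist status from a person told of a delayed start.

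The primary question is answered through the time-by-group interaction, so T1 carries the same weight as T2 or T3. If one arm's T1 mean moves because its members know their allocation, and the movement has gone or changed by T2 and T3, the difference appears as a time-by-group effect with no contribution from treatment. It could inflate or mask a real effect, depending on its direction. The contrasts at stake are CBT versus waitlist and MBSR versus waitlist.

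**Working it through.** **1. Order of steps.** Participants and recruitment runs: pre-screening, information and consent, random assignment, description of what the waitlist is told. T1 is not mentioned before assignment. Study design places T1 just before the intervention and refers to it by arm. No sentence places T1 ahead of allocation or makes release of the allocation depend on T1. No sentence dates the waitlist notice relative to T1 either. The text therefore favours T1 after allocation and leaves disclosure before T1 open.

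**2. The plan's own sample size.** I used the noncentral F for the multivariate interaction with 3 groups and 3 times: s = 2, df1 = 4, df2 = 2(N − 3), λ = 2·N·0.25².

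- N = 151: df2 = 296, λ = 18.875, power .9500 (N = 150 gives .9486).
- N = 98: df2 = 190, λ = 12.25, power .8005.

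Both stated totals reproduce. They supply the arm sizes of about 50 and 33 used below.

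**3. Size of the effect if a shift occurs.** Assumptions that are not in the documents: no true treatment effect; a shift of d SD in the waitlist arm at T1 only; equal variances; a common correlation ρ between occasions.

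*Pairwise contrast of T1-to-T2 change, active versus waitlist.* The SD of change is √(2(1 − ρ)), which is 1 SD at ρ = .5. With 50 per arm, SE = √(2/50) = 0.20 SD. The noncentrality is d/0.20 = 0.5, 1.0 and 1.5 on 98 df.

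*Three-by-three interaction as planned, univariate test.* The squared interaction effects sum to (2/3)(2/3)d² = (4/9)d², so λ = n(4/9)d²/(1 − ρ). With n = 50 and ρ = .5, λ = 0.44, 1.78 and 4.00 on 4 and 294 df.

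False-positive rate at a nominal 5%:

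| n per arm | ρ | Test | d = 0.1 | d = 0.2 | d = 0.3 |
|---|---|---|---|---|---|
| 50 | .5 | pairwise change | 7.9% | 16.8% | 31.8% |
| 50 | .5 | interaction | 7.3% | 15.4% | 31.5% |
| 50 | .7 | interaction | 8.9% | 23.8% | 51.0% |
| 33 | .5 | interaction | 6.5% | 11.4% | 21.3% |
| 33 | .7 | interaction | 7.5% | 16.5% | 34.2% |

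**4. What drives these figures.** Only the difference between the shift at T1 and the shift at T2 or T3 enters the interaction. If the waitlist reaction persisted unchanged, d would cancel and the rate would stay at 5%.

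**The case against.** **The key step is inferred.** A reader might conclude that the article says waitlist members are told before T1. It does not: the notice carries no timing, and bias needs disclosure before T1, not just allocation before T1. The by-group wording for T1 is also an ordinary way to say that all arms are measured, and the design figure, which may settle the order, was not available. This stands, and it limits the point to what the wording suggests and fails to protect. It does not remove the point, because the article does set out its enrolment sequence and that sequence runs from consent to allocation without T1.

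**A shift need not bias anything.** Waitlist members still know their status at T2 and T3. A reaction that persists equally cancels from the change when T1 follows disclosure, and would enter the change in full if T1 came first. This also stands: the figures apply only to a shift that does not persist equally. A T1 taken before allocation is at least an uncontaminated baseline. Knowing one's arm at T2 and T3 is a separate limit of any waitlist control.

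**Scope.** CBT versus MBSR, which the trial's hypotheses include, is untouched, since both programmes are presented alike. Conceded.

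**Loss before T1.** It is tempting to add that reordering would rescue people who leave between assignment and T1. It would not in general: most of them would lack T2 and T3 as well, and a complete-case repeated measures ANOVA would exclude them in either order. They also already have a screening measurement of both primary outcomes.

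**Conclusion.** The concern holds in a limited form. The text points to T1 being collected after allocation, and nothing stated prevents waitlist members from knowing their arm when they complete it. The blinding described does not cover this, so the article's assurance that expectation effects are minimal is not supported for the waitlist contrasts.

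If a waitlist-only shift of 0.1, 0.2 or 0.3 SD were present at T1 and gone afterwards, the false-positive rate with 50 per arm and ρ = .5 would be about 7–8%, 15–17% or 32%. It would be lower with 33 per arm and higher with a stronger correlation. The shift, its transience and the correlation are all assumptions; the documents show neither that such a shift occurs nor how large it would be. They also do not establish that disclosure comes before T1. The change is worth making because the exposure concerns both primary outcomes and is easily removed.

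**What to change.** - Have T1 completed before randomisation, or have the online platform release the allocation and start date only once T1 has been submitted. State this in one sentence. If the design figure or full protocol already has this order, it is enough to say so in the text.
- For any round already run in the other order, add a sensitivity analysis of T2 and T3 detachment and burnout adjusted for the screening scores of the same outcomes. These predate allocation. Note that they were also used for selection, so some regression to the mean is expected; it should be similar across randomised arms.
- Limit the statement on expectation effects to the comparison of the two active programmes.

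The cost is a reordering of online steps, a few sentences and one extra analysis where it applies. No additional participants or questionnaires are needed.

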#### Background variables

In the pre-screening questionnaire, participants will be asked to provide some basic demographic data (i.e., gender, age, the highest level of formal education and family status), basic information regarding their work (i.e., employment status, type of work, weekly working hours, tenure, leadership status and whether they are currently on sick leave) as well as some intervention-related data (i.e., willingness to dedicate enough time to the intervention, access to the internet, self-rated competency to use a computer, involvement in other forms of psychotherapy/psychoeducation, prescription of drugs to treat mental illnesses and the presence of a mental illness diagnosis).

In the questionnaire that will be administered at T2 (directly after the intervention), they will additionally be asked to report any significant work- (e.g., switching jobs), private life- (e.g., switching apartments), or intervention-related (e.g., participating in other interventions, aimed at improving mental health) changes during the last 6 weeks. They will also be asked to rate their overall satisfaction with the intervention, their attitudes towards the exercises, their previous experience with similar exercises, and their self-reported adherence to the intervention procedure.

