#### Effect evaluation

The analyses will be carried out with SPSS [88] and Mplus [89]. The significance level used in the analyses will be .05. The main research questions (i.e., group differences in psychological detachment from work and burnout) will be analyzed with two separate two-way repeated measures analyses of variance (ANOVAs), with time as the within-subjects factor (3 levels: pre, post, follow-up) and group as the between-subjects factor (3 levels: CBT, MBSR, control), for each of the main outcomes separately. Significant interactions will be followed up with a simple effects’ analysis, using the Bonferroni correction to adjust for multiple testing.

The effects of the intervention on the secondary outcomes (i.e., general and work-related well-being) will be analyzed with a two-way repeated-measures MANOVA, with time as the within-subjects factor and group as the between-subjects factor. This analysis is contingent upon moderate correlations between the dependent variables [90]. Therefore, we will first examine correlations between the secondary outcome variables. Significant interaction effects will be followed-up with ANOVAs for each of the dependent variables and a discriminant descriptive analysis to further examine the effects. The moderation (i.e., supervisor support for recovery, work-home integration supplies, unfinished tasks, time pressure) and mediation (i.e., mindfulness, work-related maladaptive thinking patterns) effects will be analyzed using the PROCESS macro for SPSS [91]. T2 measures of the studied mediators will be utilized in these analyses. In order to explore both; the inter-individual variability and the intra-individual patterns of change trajectories in the mechanisms and the main outcomes during interventions, growth curve analyses will be conducted using data from the weekly questionnaires.

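### Gender is the blocking factor in the randomisation but is not carried into the two-way primary and secondary models; the cost is small and falls on between-group contrasts at T2 and T3

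*Protocol article*

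**What the plan says.** Participants and recruitment (protocol article): "block randomization based on gender will be used", so that each of the three arms receives the same number of women and men. The reason given is "because women exhibit more rumination and difficulties detaching from work at home". Detachment is one of the two primary outcomes; burnout is the other.

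Background variables: the pre-screening questionnaire records "basic demographic data (i.e., gender, age, the highest level of formal education and family status", so gender is known before randomisation.

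Effect evaluation: the primary outcomes "will be analyzed with two separate two-way repeated measures analyses of variance (ANOVAs), with time as the within-subjects factor" and "group as the between-subjects factor (3 levels: CBT, MBSR, control), for each of the main outcomes separately". The next step is stated as: "Significant interactions will be followed up with a simple effects’ analysis, using the Bonferroni correction to adjust for multiple testing". The secondary outcomes "will be analyzed with a two-way repeated-measures MANOVA, with time as the within-subjects factor and group as the between-subjects factor". For moderation and mediation, the article says that the "effects will be analyzed using the PROCESS macro for SPSS"; it lists moderators and mediators but no covariates. The growth curve analyses of the weekly data also name none.

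Gender therefore shapes the allocation but has no stated role in any analysis.

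**The concern.** When randomisation is balanced within strata, the difference between arms no longer varies because of the stratum. If the model omits the stratum, its variance still sits in the residual. The estimated standard error is then larger than the true one, the test runs slightly below its nominal level, and some power is lost. The randomised comparison is not biased.

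The ANOVAs and the MANOVA are not left open here: calling them two-way and naming both factors excludes gender. The protocol's hypotheses compare CBT with MBSR and with control at T2 and at T3, and the simple-effects step is where such single-time comparisons would be made. The question is how much they lose, and whether the primary interaction test loses anything.

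**Working it through.** **1. The plan's own figure.** Inputs from Sample size calculation: f(V) = .25, alpha = .05, 3 groups, 3 time points, power .95 or .80. For the within-between interaction of a repeated-measures MANOVA, s = 2, df1 = (3 − 1)(3 − 1) = 4, df2 = 2(N − 3) and λ = 2·N·f(V)².
- N = 151: df2 = 296, λ = 2 × 151 × 0.0625 = 18.875, power .9500.
- N = 98: df2 = 190, λ = 2 × 98 × 0.0625 = 12.25, power .8005.

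Both stated sample sizes reproduce exactly, and neither uses gender.

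**2. Assumptions.** The documents give no gender difference. Assumed: a stable gap d of 0.2 to 0.5 SD (SD within gender), 50% or 80% women in each arm, 50 per arm, within-person correlation 0.5, and effects against control of 0.4 SD (CBT) and 0.2 SD (MBSR).

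**3. Variance explained by gender at one time point.** With p the proportion of women and v = d²p(1 − p):
- R² = v/(1 + v)
- standard error ratio, unadjusted to adjusted = √(1 + v)
- unadjusted N equivalent to 151 adjusted = 151(1 + v)

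| d | women | v | R² | SE ratio | equivalent N |
|---|---|---|---|---|---|
| 0.2 | 50% | 0.0100 | 1.0% | 1.005 | 152.5 |
| 0.5 | 50% | 0.0625 | 5.9% | 1.031 | 160.4 |
| 0.2 | 80% | 0.0064 | 0.6% | 1.003 | 152.0 |
| 0.5 | 80% | 0.0400 | 3.8% | 1.020 | 157.0 |

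**4. CBT against control at T2, by formula (normal approximation, 50% women).** The standardised effect is 0.4/√(2/50) = 2.00. Omitting gender in effect raises the critical value from 1.960 to 1.960 × SE ratio.
- With gender: power Φ(2.00 − 1.960) = .516.
- Without, d = 0.2: critical value 1.970, power .512 (0.4 points lower), type I error .049.
- Without, d = 0.5: critical value 2.020, power .492 (2.4 points lower), type I error .043.

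If Bonferroni is applied over three pairwise comparisons (an assumption about the family), the critical value is 2.394. Power with gender is .347; without it, .342 (d = 0.2) and .320 (d = 0.5), a loss of 0.4 and 2.7 points.

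**5. Simulation** (4,000 runs, 3 × 50, gender balanced across arms, each test at .05, 50% women). Power without / with gender:

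| scenario | time × group | CBT v control at T2 |
|---|---|---|
| d = 0.2, stable | .415 / .414 | .500 / .504 |
| d = 0.5, stable | .426 / .425 | .486 / .513 |
| d = 0.2, gap 0.2 SD wider after T1 | .411 / .414 | .498 / .512 |
| d = 0.5, gap 0.2 SD wider after T1 | .414 / .418 | .457 / .507 |

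The interaction power is below the plan's .95 because the effects assumed here are smaller than those implied by f(V) = .25; only the differences within a cell matter.

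Under the null, over all scenarios including 80% women, the interaction test rejects at .045 to .053 with or without gender. The T2 contrast without gender rejects at .037 to .052.

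**6. Why the interaction test is spared.** It uses differences between time points within a person. A gender effect that is the same at T1, T2 and T3 is subtracted out. Only a gender-by-time effect could remain, and an assumed 0.2 SD shift costs at most 0.4 points. Within-arm comparisons over time are spared from a stable effect for the same reason.

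**The case against.** The strongest reply is that the planned gatekeeper is the time-by-group interaction, which loses nothing from a stable gender effect, and that single-time contrasts arise only after it is significant. The stated purpose of the blocking is equal numbers of women and men per arm. That balance is achieved at randomisation whether or not gender is modelled, and the article claims no precision gain. The gender gap is unquantified, and because entry requires at least moderate difficulties with detachment and burnout, it may be narrower among those enrolled than among employees at large. What error there is goes in the conservative direction. All of this stands, and it is why the point is minor. It does not remove the mismatch between design and model, nor the small loss in the contrasts at T2 and T3.

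Three stronger readings are tempting, and the documents do not carry them:
- A reader might infer that every planned analysis leaves gender out. This is firm only for the ANOVAs and the MANOVA. For PROCESS and the growth curves the article is silent on covariates, which a separate analysis plan may list; gender also appears in the part of the Measures headed as moderators and control variables.
- A reader might infer that the benefit of blocking is lost. The balance at randomisation is kept, and the primary test is barely touched.
- A reader might infer that the protocol declares gender prognostic throughout and that the mediation results are therefore confounded. The stated link covers rumination and detachment only, not burnout, mindfulness, maladaptive thinking or the secondary outcomes. A gap of 0.4 SD in both mediator and outcome would produce a spurious slope of 0.16p(1 − p)/(1 + 0.16p(1 − p)), which is .033 at 70% women and .038 at 50%. The gap in the mediators is purely an assumption.

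**Conclusion.** The point holds as a minor one. The blocking factor is absent from the primary and secondary models as the article fixes them. The primary time-by-group test is essentially unaffected: power differs by .001 for a stable gap with 50% women.

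For between-group simple effects at T2 and T3, a stable gap of 0.2 to 0.5 SD with 50% women means that gender explains about 1% to 6% of variance, standard errors are about 0.5% to 3% too large, power is about 0.4 to 3 points lower, and the type I error is nominal to slightly below .05. The loss is smaller with 80% women. It reaches 5 points only if the gap is 0.5 SD at baseline and widens by a further 0.2 SD.

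The gap, the gender mix, the within-person correlation and the treatment effects are all assumptions. There is no inflation of false positives and no bias in the randomised comparisons.

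**What to change.** Under Effect evaluation, state that gender, as the blocking factor, enters both primary repeated-measures ANOVAs, the secondary MANOVA and its follow-up ANOVAs as a main effect and as gender-by-time, and that the simple effects are taken from these adjusted models. Gender should be centred, so that the time and group terms refer to the average participant.

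As a low-cost option, also enter gender as a covariate in the PROCESS mediation models, because the mediator-outcome path is not randomised and blocking does not protect it.

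The cost is wording and, for two gender categories and three time points, one degree of freedom for the main effect and two for the interaction with time. No new data are needed and the sample size does not change. The wording is best fixed before outcome data are seen.
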